### Routine exercise

Subjects allocated to the control group will not receive any specific training from the study schedule. They will be requested to keep their original habit of routine exercise (except Tai Chi) such as walking, dancing, cycling, and so on, and they will also be requested to practice for 1 hour at a time, 3 times a week in the training period as well as the follow-up. The follow-up training for both groups will be monitored by phone call.

### Assessment procedures

Data from patients and caregivers will be collected at baseline (T0), 2 months (T1) and 8 months (T2) by 2 research assistants. Another 3 selected and trained occupational therapists will score the BBS, TUG, 6MWT, UPDRS-III and PDQ-39 in an activity that is video- recorded by the assessor. The data collected from the assistants and therapists will be entered in a dedicated computer and kept in a secure and lock-protected location. All assessors and scorers are blinded for group allocation and each participant will be followed up by the same assessor. To test the quality of home-based routine exercise, patients and caregivers will fill in all self-report records. Observational tests or measures that follow a semi-structured interview format will be conducted in the patient’s home environment by the assessor. Considering possible response fluctuations in PD, measures will be administered 1 hour after medication intake (the ‘ON’ phase). For budgetary reasons, the 6-month follow-up training will be monitored by phone call and the data for assessment will be finally collected by the same assessor.

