## Methods and Design

### Trial design

A single-blind (assessors), parallel randomized controlled trial will be conducted to compare Tai Chi with routine exercise (allocation ratio 1:1). The study period is 8 months including a 2-month supervised intervention and a 6-month follow-up with the primary outcome measured at baseline, 2 and 8 months. The primary site for conduct of the study, including all study visits and Tai Chi interventions will be conducted at the Affiliated Hospital of Jining Medical University, Jining, Shandong, China. Routine exercise will be conducted in a home-based environment.

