### Outcome measures

#### Primary outcome measures

All participants will be measured before commencing each intervention (pre-test) and upon completion (post-test). The primary outcome measure includes the Berg Balance Scale (BBS), Timed Up and Go Test (TUG) and Six-Minute Walk Test (6MWT), which are known to be valid and reliable clinical instruments [22]. According to the wide disability spectrum associated with PD, balance impairments are common in patients [23]. The BBS will be utilized to identify potential training effects on balance [24]. Functional gait performance will be measured by the TUG [25]. Participants will be asked to walk as quickly as they safely can under all conditions and will be permitted to use their usual gait aid. The TUG measures a participant’s ability to perform sequential gait movements and has been proved to be a reliable outcome measure for use in PD. In addition, the 6MWT will be completed to quantify walking capacity, measured as the distance covered in which conducted on a 20-meter walkway next to the laboratory and we record total distance traveled. This test has demonstrated high reliability in people with PD [26]. Assessment will be performed during the patient’s self-reported optimal ‘ON’ period, often 1 hour after medication.

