### Follow-up evaluation

Physical activities and other leisure time activities will be measured during the 6 months follow-up via telephone interviews. This is to monitor changes among participants in activities that can enhance performance on tests, apart from Tai Chi and routine exercise. The self-completed quality of life questionnaire will be mailed to participants after 2 months from randomization. All baseline measurements will be repeated at 6-month follow-up. Researchers performing all measurements will be blinded to group allocation and participants will be required not to reveal to researchers which group they were in (Table 1).

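### Home visits by the outcome assessor contradict the rule that all study visits are at the hospital, leaving the test setting unfixed and the assessor blinding exposed

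*Protocol article*

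**What the plan says.** Three sections of the protocol article say where assessments take place.

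- Trial design: "including all study visits and Tai Chi interventions will be conducted at the Affiliated Hospital of Jining Medical University". Only routine exercise is assigned to the home.
- Primary outcome measures: the 6MWT is "conducted on a 20-meter walkway next to the laboratory". No place is given for the BBS or TUG.
- Assessment procedures: "Observational tests or measures that follow a semi-structured interview format will be conducted in the patient’s home environment by the assessor". The same paragraph says that three therapists "will score the BBS, TUG, 6MWT, UPDRS-III and PDQ-39 in an activity that is video- recorded by the assessor".

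On blinding, Assessment procedures states that "All assessors and scorers are blinded for group allocation and each participant will be followed up by the same assessor". Follow-up evaluation adds that "participants will be required not to reveal to researchers which group they were in". Trial design describes the trial as single-blind, with the assessors as the blinded party.

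**The concern.** An assessor's visit to the patient's home cannot be squared with a rule that every study visit is at the hospital. Two things depend on how this is resolved.

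The first is measurement. The primary analysis compares change in BBS between arms. Balance and gait scores can depend on floor, chair and available space, so the setting should be the same for everyone. ANCOVA on baseline BBS does not remove a setting shift that arises after baseline.

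The second is blinding. Patients know their treatment, so assessor blinding is all the trial has. A home can show which arm a patient is in, and because the same assessor stays with each participant, anything learned at one visit is carried to the next.

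**Working it through.** The plan gives no figure on setting, so the check is first textual and then an illustration under stated assumptions.

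**Step 1. What the home sentence can mean.**

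- *Reading A: it covers BBS, TUG or UPDRS-III.* In favour: it stands in the section on outcome assessment, these are observed performance tests, the assessor named is the one who records the scored activity, and no other section fixes where they are done. Against: no test is named, and the semi-structured interview qualifier may govern both nouns.
- *Reading B: it covers only interviews or checks of home exercise.* In favour: the preceding sentence concerns the quality of home-based routine exercise.

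The next sentence, on timing after medication, does not settle the matter. It is a general rule that also appears under the outcome measures, and it says nothing about place. Under either reading the assessor goes to the home, which contradicts Trial design.

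**Step 2. Reading A: possible size.**

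Inputs from Sample size: BBS difference 4.0, SD 7.2, 116 patients, so 116/2 = 58 per arm. Not in the documents, and therefore assumed: a setting shift s of 1–2 BBS points at T1, and a difference Δp of 0.20–0.40 between arms in the share tested at home.

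- Bias = s × Δp
- Standard error of the arm difference = 7.2 × √(2/58) = 1.337
- Two-sided type I error = 1 − Φ(1.96 − bias/1.337) + Φ(−1.96 − bias/1.337)

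| s | Δp | Bias | Share of 4.0 | Type I error |
|---|---|---|---|---|
| 1 | 0.20 | 0.2 | 5% | 5.3% |
| 1 | 0.40 | 0.4 | 10% | 6.0% |
| 2 | 0.20 | 0.4 | 10% | 6.0% |
| 2 | 0.40 | 0.8 | 20% | 9.2% |
| any | 0 | 0 | 0% | 5.0% |

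If the share is equal in both arms, only noise remains. With a 50/50 mix the SD becomes √(7.2² + 0.25 s²), which is 7.217 for s = 1 and 7.269 for s = 2. Power at 58 per arm (normal approximation) falls from 84.9% to 84.7% and 84.2%. That 58 per arm gives more than the stated 80% power is a separate matter and does not affect this point.

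**Step 3. Reading B: what an assessor could see, and when.**

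- T0: the baseline test precedes opening of the envelope (Randomization), so nothing can be revealed.
- T1: control homes may hold the records of home-based routine exercise. The Tai Chi videotape is given out only after the 2 months of training.
- T2: Tai Chi homes may hold the videotape and the logs of home practice.

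Exposure is therefore greatest at T2 and smaller at T1, the end-of-treatment visit on which the primary analysis rests.

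**The case against.** Several stronger conclusions are tempting, and the documents do not support them.

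- *A reader might infer that the primary outcome tests are placed in the home.* The sentence names no test. For the 6MWT the place is fixed on the laboratory walkway, and no home version is described. The conflict bears mainly on the BBS, TUG and UPDRS-III, and for these only under Reading A.
- *A reader might infer that the arm contrast is biased, because Tai Chi patients attend the hospital three times a week and controls do not.* Nothing makes the place of testing depend on class attendance. The sentence carries no condition on arm. Taken literally it applies to every patient alike, and baseline setting cannot depend on an allocation not yet made. This part of the objection stands: bias is possible, not shown.
- *A reader might infer that the primary comparison is unblinded.* The videotape arrives only after training ends. Control exercise is a continuation of existing habits such as walking or cycling, so seeing it would not clearly identify the arm. Separate blinded therapists do the scoring, and participants are asked not to disclose their group. These are real safeguards, but partial ones. The request is addressed to participants and does not mention caregivers, who also supply data. If the scored activity is filmed at home, the scorers may see the same surroundings.

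It can also be said that an article need not list the location of each test. That is fair for missing detail, but here the article states two locations that cannot both hold.

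**Conclusion.** The contradiction between Assessment procedures and Trial design is certain and holds under either reading; the fit with the walkway specified for the 6MWT is poor. Its consequences are conditional. If performance tests are meant, mixed settings add noise that costs under one percentage point of power for a shift of 1–2 BBS points. They bias the treatment effect only if setting differs by arm. The 0.2–0.8 point range and the type I error of 5.3–9.2% rest wholly on the assumed shift and the assumed difference between arms, and are not estimates from the documents. If only interviews or exercise checks are meant, the effect is a plausible but undemonstrated weakening of the assessor blinding, chiefly at T2. The point still merits correction because it touches measurement of the primary outcome and the trial's only blinding, and a setting that is not recorded cannot be adjusted for afterwards.

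**What to change.** Reconcile Trial design, Primary outcome measures and Assessment procedures by replacing the home sentence with text to this effect:

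- BBS, TUG, 6MWT and UPDRS-III are performed at the hospital, in the same setting for both arms, at T0, T1 and T2.
- Outcome assessors make no home visits.
- Home exercise is followed through the self-report records and phone calls already planned, handled by staff who do not assess outcomes.

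Trial status reports that recruitment is under way, so the setting of each assessment already done should also be recorded, so that any mixture can be described by arm and visit.

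The cost is a sentence or two in the protocol and the assessors' instructions, since hospital visits are already planned. The one downside is small: a patient who cannot travel will have a missing value at that visit instead of a home score that may not be comparable.

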### Statistical analysis

#### Baseline analyses

The assessment of demographic characteristics of participants at baseline will compare the participants who are subsequently randomized and those who are screened but not randomized. Exclusion from randomization will be tabulated by a specific criterion.

### Efficacy analysis of outcome measures

The primary analysis will compare the changes on BBS from baseline to endpoint of treatment between two treatment groups using analysis of covariance (ANCOVA) adjusting by the BBS baseline value. The statistically significant level of *P*-value is less than 0.05. If any participants drop out from the trial, intention-to-treat analyses will be adopted. Participants who withdraw will be treated as having no change from baseline at all times after dropping out. In addition to intention-to-treat analyses, multiple imputation will be used to perform secondary analyses. We will also check the mechanism of the participation drop-out and determine whether the missing data is ignorable or not. If non-ignorable missing data methods are needed, we will explore both selection and pattern-mixture types. All efficacy analyses of primary and secondary outcome measurements will be conducted by the same analytical strategy.

All participants will undergo sub-group analysis test for potential effect modification for the presence of a spouse/carer on the therapeutic effect. Appropriate adjustments will be made in the statistical analyses for potential factors which are unevenly distributed between the two groups. Participants with significantly impairment of balance, gait and quality of life at baseline will be analyzed to determine the independent impact of these disturbances on the therapeutic effect. Adjusted estimates will be obtained by identifying baseline imbalances and incorporating them into a regression model by pre- and post-intervention primary outcome scores. If normal distribution assumptions were not met, non-parametric analysis will be adopted even after suitable transformations.

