## Background

Parkinson’s disease (PD) is a common neurodegenerative disorder that is associated with four landmark symptoms of resting tremor, bradykinesis, rigidity and decreased postural reflexes [1]. Globally, there are at least 4 million people estimated to be diagnosed with PD [2]. Although the specific causes of PD are unknown, incidence increases with age, especially after 50 years old [3]. In China, PD prevalence is 1.70% in people aged more than 65 years old [4]. It is reported that in people with PD it is common to develop a slow, shuffling and dysrhythmic gait [5]. Also, most people with PD will ultimately develop impaired balance [6]. Despite advances in medical care, gait disturbance and balance decrements worsen as the disease progresses, contributing to loss of independence, falls and poor quality of life [7]. Therefore, people with PD gradually place a strain on societies, healthcare and financial systems.

Exercise, as one of non-pharmacological interventions in assisting the treatment of PD, has demonstrated efficacy in improving gait disturbance, balance decrements and frequency of falls in patients with PD [8-10]. It may improve brain health by suppressing oxidative stress, stabilizing calcium homeostasis and plasticity-related changes in the central nervous system including enhanced glucose utilization, synaptogenesis, angiogenesis and neurogenesis [11-14]. Also, there is supporting evidence indicating that intensive exercise is more effective in controlling balance and gait for PD in relevant studies [15]. However, the prevalence of older Chinese people using such exercises is quite low. As an important component of traditional Chinese *Qigong* exercises, Tai Chi is an ancient art and science of healthcare that is quite popular with Chinese older adults.

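### Counting every withdrawal as zero change in the main analysis can bias the estimated effect, and the analyses for non-ignorable drop-out depend on a question that observed data cannot settle

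*Protocol article*

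**What the plan says.** In the protocol article, Efficacy analysis of outcome measures, the primary comparison is the change in Berg Balance Scale (BBS) from baseline to the end of treatment, by ANCOVA with baseline BBS as covariate. For missing outcomes the section sets four things:

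- The main, intention-to-treat analysis uses a single fixed value: "Participants who withdraw will be treated as having no change from baseline at all times after dropping out".
- The alternative is ranked below it: "In addition to intention-to-treat analyses, multiple imputation will be used to perform secondary analyses".
- The drop-out mechanism is to be examined: "We will also check the mechanism of the participation drop-out and determine whether the missing data is ignorable or not". What follows is conditional: "If non-ignorable missing data methods are needed, we will explore both selection and pattern-mixture types".
- The scope is wide: "All efficacy analyses of primary and secondary outcome measurements will be conducted by the same analytical strategy". The rule therefore also reaches TUG, 6MWT, UPDRS-III and PDQ-39.

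The Sample size section uses a difference of 4.0 BBS points and an SD of 7.2, and anticipates 20% drop-out with 71 patients per group. The Background states that "gait disturbance and balance decrements worsen as the disease progresses" and ends with the hypothesis that Tai Chi improves balance more than routine exercise.

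**The concern.** Zero change is a statement about what patients who leave would have scored. It is neutral only if their mean change would be zero in each arm. The protocol gives no reason to expect that: it hypothesises improvement with Tai Chi and describes worsening over the course of the disease.

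Two things are at stake. First, the headline estimate may not describe the effect in all randomised patients. It shrinks if drop-out is equal and Tai Chi works. It can shift either way if drop-out differs between hospital classes three times a week and habitual exercise at home. Second, the analyses that would show how far the result depends on the missing values may never be run, because they wait for a finding on ignorability.

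**Working it through.** **Inputs.** Difference 4.0, SD 7.2 (variance 51.84), 71 per arm and 20% drop-out are from the Sample size section.

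**Assumptions.** The 7.2 is the SD of change (the article does not say). Drop-out is completely at random, and all of the 20% is missing at T1. Baseline adjustment does not reduce the variance. Control mean change is 0 unless stated.

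**The plan's own figure.** 2 × (1.960 + 0.842)² × 51.84 / 16 = 50.9, so 51 per arm or 102 in total, against the 116 stated. That mismatch is a separate matter, and nothing below uses the 116.

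**1. Estimate under the zero-change rule.** If a fraction d is missing at random and set to 0, the expected mean change in an arm is (1 − d) × μ. With d = 0.2 in both arms: 0.8 × 4.0 − 0.8 × 0 = 3.2, which is 0.8 points too small for the effect in all randomised patients.

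**2. Standard error.** The variance of change in an arm becomes (1 − d) × 51.84 + d(1 − d) × μ².
- Control: 0.8 × 51.84 = 41.47.
- Tai Chi: 41.47 + 0.16 × 16 = 44.03.
- SE = √((41.47 + 44.03) / 71) = 1.10; the mean model SE in simulation is 1.09.
- Complete data: 7.2 × √(2/71) = 1.21.
- Completers only (0.8 × 71 = 56.8 per arm): 7.2 × √(2/56.8) = 1.35.

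**3. Coverage of 4.0.** The bias in SE units is 0.8 / 1.10 = 0.73. Coverage ≈ Φ(1.96 − 0.73) − Φ(−1.96 − 0.73) = 0.89. Simulation gives 88.5% to 88.9%; an observed-data analysis gives about 95% under this drop-out.

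**4. Source of the undercoverage.** In simulation the mean model SE of the zero-change estimator (1.09) matches its sampling SD, and its interval covers its own mean, 3.2, 95% of the time. The shortfall for 4.0 is therefore the dilution.

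**5. Type I error, no true difference.** If both arms change by c, the false difference has size c × |d₁ − d₂|.

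| Drop-out | Common change c | False difference (size) | Type I error |
|---|---|---|---|
| 20% / 20% | 0 or 4 | 0 | about 5% |
| 10% / 30% | 0 | 0 | about 5% |
| 10% / 30% | 2 | 0.4 | about 7% |
| 10% / 30% | 3 | 0.6 | about 8–9% |
| 10% / 30% | 4 | 0.8 | about 11% |
| 15% / 25% | 3 | 0.3 | about 6% |

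Example, 10%/30% with c = 3: variance sum = 0.9 × 51.84 + 0.09 × 9 + 0.7 × 51.84 + 0.21 × 9 = 85.64; SE = √(85.64/71) = 1.10; shift = 0.6/1.10 = 0.55; two-sided rejection ≈ 8.5%. If both arms gain, the arm that loses more patients looks worse; if both decline, it looks better. The unequal splits and the common changes are illustrations and are not in the protocol.

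**6. The trigger.** Non-ignorable missingness means that drop-out depends on the unseen values even after conditioning on what was seen. Observed data fit an ignorable model and suitably chosen non-ignorable models equally well, so a plan to "determine whether the missing data is ignorable or not" cannot be carried out from the data without assumptions that cannot be tested.

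**The case against.** Several stronger readings are tempting, and the documents do not support them.

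- **A reader might infer that the rule understates the variance, as a second fault beside the bias.** It does not: the SE is right for the estimator it belongs to (step 4). Setting 1.10 against 1.35 compares estimators with different targets, and the ratios of estimate to SE are nearly equal (3.2/1.10 = 2.9; 4.0/1.35 = 3.0). Power hardly moves: 82% against 83% in simulation. What remains is narrower. An SE below the 1.21 of complete data should not be read as the precision for the effect in all randomised patients.
- **A reader might infer a generally inflated false-positive rate.** The protocol gives one drop-out figure, not a split by arm. With equal drop-out, type I error is about 5%, and a real benefit is shrunk rather than exaggerated. The 7–11% needs a marked imbalance together with a sizeable common change. Controls receive no specific training, and no control gain is quantified.
- **A reader might lean on disease progression.** The Background speaks of the course of the disease, while the primary comparison comes after 2 months on stable medication. The argument has more force at the later follow-up, which is not the primary comparison.

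The plan also already contains multiple imputation and names both classes of non-ignorable model, so dependence on the zero rule might become visible. It does not prescribe a formal test of ignorability; it says only that the mechanism will be checked. Making the intention-to-treat analysis conditional on drop-out occurring is a minor point of wording.

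These objections reduce the size of the problem. They leave a main analysis that is biased whenever the mean change of those who leave is not zero, and a sensitivity analysis that may be skipped.

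**Conclusion.** The point holds in limited form and should be fixed. Under the protocol's own effect, SD and drop-out figures, the main estimate would be about 3.2 instead of 4.0, with about 89% coverage of 4.0, all of it attributable to dilution. The size scales with the fraction missing at T1: 10% in each arm would give 0.9 × 4.0 = 3.6. A spurious difference needs both unequal drop-out and a common non-zero mean change, and its direction is not fixed. The figures rest on random drop-out and on 7.2 being the SD of change. The objection to the ignorability trigger needs no figures.

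**What to change.** 1. State that all randomised patients are analysed as allocated, whether or not anyone drops out.
2. Make the primary analysis either the multiple imputation already planned, done separately by arm, or a baseline-adjusted mixed model for repeated measures on T1 and T2 with the contrast at T1. Either is acceptable; both assume missingness at random, which is why item 4 is needed.
3. Keep the zero-change rule as a sensitivity analysis.
4. Replace the conditional step by a pre-specified delta-adjusted pattern-mixture (tipping-point) analysis that is always run and reported.

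The cost is revised wording and a little more programming. No new data or patients are needed. The reported SE will be larger, about 1.35 for completers against 1.10 in the example, with almost no loss of power when drop-out is equal.
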